**A. Purpose of Protocol**

In this study, we will test whether placebo pills that are truthfully described “as inert substances (placebos), like sugar pills, that have been shown in rigorous clinical tests to somehow produce significant self-healing processes in IBS patients” given in a context of positive expectation and reassurance can produce clinical improvement in patients with IBS. This study is a three-week RCT comparing non-deceptive open label placebo treatment to an observation waitlist control in 80 IBS patients. We believe this study involves no ethical compromise from normative ethical standards and could potentially result in innovative treatment strategy for IBS patients as well as improve our understanding of the placebo effect in clinical trials. This study will ultimately give us preliminary data to support a more rigorous NIH RO1 grant.

**B. Significance and Background for the Study**

1. Significance:

Clinical trials suggest that patients respond to placebo in clinically significant and meaningful ways. Recent basic science research has shown that placebo treatment has a biochemical and neurobiological basis of action similar to that of some pharmacological agents. (Miller & Kaptchuk 2008, Benedetti et al 2005, Pacheco-Lopez et al 2006). But the use of placebo in clinical practice is considered unethical because it involves deception of patients and thus is contrary to informed consent. Currently the effectiveness of placebo randomized controlled trials (RCT) is believed to depend on concealment such that patients believe they may be on a real medication. We are challenging this assumption that placebo is only effective when concealed or involving deception. We hypothesize that open-label non-deceptive administration of an inactive (placebo) pill in the context of patient-practitioner relationship of education, reassurance, positive expectation and confidence can elicit positive clinical outcomes in IBS patients. We propose a RCT to examine whether the non-deceptive administration of placebo pill can improve symptoms in patients with IBS beyond a no treatment waitlist control. The significance and background section below discusses the following issues: 1. placebo responses in RCTs in general and specifically in IBS; 2. mechanistic advances in placebo research including IBS; 3) ethical issues and the use of placebo; 4) a theoretical model of how the components of the placebo response -- including positive expectation, conditioning, adherence effects and a supportive patient-physician relationship --- that do not necessarily require deception and 5) preliminary data suggesting non-deceptive placebo administration can elicit clinical improvement in patients.

2. Placebo Responses in Clinical Medicine:

Clinical research continues to demonstrate that patients in the placebo control arm of RCTs can have dramatic improvements. For example, recent meta-analyses on Parkinson’s disease (Goetz at al 2000), asthma (Joyce et al 2000), social phobia (Oosterbaan et al 2001), migraine (van de Kuy et al 2002), chronic fatigue syndrome (Cho et al 2005), symptom management (e.g., as pain and appetite) in oncology patients (Chvetzoff and Tannock 2003), sleep disorders (McCall et al 2003), restless leg syndrome (Fulda & Wetter 2007) and chronic pain (McQuay et al 1995) have all demonstrated that the response to placebo treatment in RCTs is dramatic and can be clinically significant. In fact, the high response to placebo treatment in RCT is the presumed reason why many widely used medications with well described physiological effects–- including antidepressants; analgesics, anxiolytics, antihypertensives, hypnotics, anti-anginal agents, angiotensin-converting enzyme inhibitors, -blockers, antihistamines, and nonsteroidal asthma drugs etc. are frequently indistinguishable from placebo in well-designed RCTS. (Temple & Ellenberg 2000, cf. Walach et al 2005)

3. Placebo Responses in IBS:

Similar to other illnesses, placebo responses in clinical trials involving patients with gastrointestinal disorders are high. (Musial et al 2007) Our team has published a meta-analysis (Patel et al 2005) that found that placebo responses in IBS clinical trials ranged between 16.0 to 71.4% with a population-weighted average of 40.2%, 95% CI (35.9, 44.4). More importantly, our team recently demonstrated in a RCT (n=262) that placebo treatment (sham acupuncture) combined with an augmented patient-practitioner context produced ‘adequate relief’ of IBS symptoms in 62% of patients compared to 28% in the wait-list control group (p<0.0001) (Kaptchuk et al 2008). The magnitude of this response is not only statistically significant but also clinically significant and comparable with current FDA approved medications for IBS.

4. Mechanistic Advances in Understanding Placebo Mechanism(s):

Although the physiology of placebo effects is not completely understood, evidence clearly links the release of endogenous opioids with placebo-induced analgesia. (Levine 1978) A recent meta-analysis has shown that when naloxone, an opioid antagonist, is administered by hidden injection, placebo analgesia can be dramatically reduced or even eliminated. (Sauro, 2005) Moreover, using positron emission tomography (PET) to measure endogenous neurotransmission, Petrovic and colleagues (2002) found that both opioid analgesia and placebo analgesia increased cerebral blood flow in brain regions known to be rich in opioid receptors including such as the rostral anterior cingulated cortex (rACC). Likewise, Wager et al (2004), using functional resonance imaging (fMRI), showed that placebo cream was associated with decreased activity in pain-sensitive regions including the insula and ACC when comparing the response to noxious stimuli applied to the control. Building on these and other studies, Zubieta and colleagues (2005, 2006) observed with PET placebo-induced activation of the µ-opioid receptors-mediated neurotransmission endogenous opioid system in subjects with sustained pain.

Importantly, for our hypothesis, recent research has demonstrated that placebo analgesia is not a single entity but rather a spectrum of effects related to the divergence between conscious expectation and unconscious conditioning pathways. (Klinger et al 2006) In an elegant series of experiments, Amanzio and Benedetti (1999) were able to induce different types of placebo analgesia. For example, the placebo response to verbal expectation paired with saline injection could be completely blocked with naloxone. Likewise, morphine conditioning alone (i.e., two separate administrations of morphine without verbal expectation) also produced placebo analgesia that was naloxone-reversible. By contrast, ketorolac (a non-opioid analgesic) conditioning together with expectation produced a placebo response that was only partially blocked by naloxone while ketorolac conditioning alone produced placebo responses that were naloxone-insensitive. Other experiments have also shown that expectations and conditioning effects can be separated and then combined to produced an even greater placebo response than each alone. (Klinger et al 2006, Amanzio and Bededetti 1999) Thus, it seems that placebo responses can be parsed into different mechanisms and can involve conscious expectations and/or unconscious conditioning responses. These studies support our theoretical model that clinical placebo responses are not simply due to expectation or conditioning, but involve multiple pathways.

The recent neuro-chemical and neurophysiologic advances in general placebo effects are echoed in the mechanistic studies of placebo response in IBS patients. For example, using a rectal balloon model of inducing intestinal discomfort in IBS patients, Lieberman et al (2004) showed that placebo analgesia in IBS is related to activation of right ventrolateral prefrontal cortex and is mediated by activation of dorsal anterior cingulated (dACC), an area typical associated with pain unpleasantness. Also important for our proposed study, Vase and colleagues (2005) showed that IBS placebo analgesia does not necessarily involve endogenous opioids but may be related to non-expectation mechanisms. (Vase et al 2005)

5. Ethical Issues on Placebo Use in the Clinical Setting:

The AMA’s House of Delegates recently voted that physicians should consider adopting strategies that “produce a placebo-like effect through the skillful use of reassurance and encouragement.” (American Medical Association 2006). The report also supported the normative ethical position (e.g. Bok 1974) that “in the clinical setting, the use of a placebo without the patient’s knowledge may undermine trust, compromise the patient-physician relationship, and result in medical harm to the patient.” Despite this report, physicians continue to believe in the power of placebo. A recent study found that 96% of 466 surveyed doctors believed that placebo could help patients and up to 40% of the physicians reported that placebos could benefit patients physiologically for certain health problems (Sherman and Hickner 2007). In addition, 48% of respondents to this survey reported giving at least 1 type of treatment in a situation where there was no evidence of clinical efficacy. (Steenhuysen 2008) This study confirmed the findings of others. Hrobjartsson and Norup (2003) in a national survey of 772 Danish physicians found that 86% reported using a placebo treatment at least once within the past year, and 48% reported using placebo treatments >10 times in the past year. In a small Israeli survey (89 respondents) by Nitzan and Lichtenberg (2004), 60% of physicians and nurses reported prescribing placebos. These findings are also consistent with other earlier surveys in Great Britain, Sweden, and New Zealand (e.g. Gray and Flynn 1981, Thomson and Buchanan 1982, Lynoe et al 1993) as well as the early American study by Goodwin and Goodwin (1979). Such surveys suggest that physicians want to utilize placebo effects in clinical practice and sometimes go beyond normative ethical boundaries. These findings suggest that developing a non-deceptive option for placebo usage is an urgent ethical priority.

One potential solution to question of harnessing the placebo response is a direct challenge to the unproven belief that deception is necessary for a placebo to work. While mostly overlooked as an option, there have been such proposals in the past. The psychiatrist Walter Brown (e.g., 1994) has argued that the scientific evidence should make it possible to elicit a placebo effect without deception. In a related argument, the medical philosopher , Brody (1982) maintains that within the context of a supportive, positive, honest and reassuring clinical encounter, can elicit what we usually called placebo effect and can create an “an effective separation of deception and the placebo effect in clinical practice.” While Brody does not suggest open-label placebo is necessary, he proposes that clinical practices can elicit what he calls the “inner pharmacy.” Thus, expectation can be utilized without deceit. Certainly Brody and Brown’s position is not contradicted by more recent scientific evidence. Our experiment is a direct effort to empirically test this hypothesis.

6. Theoretical Rational for Non-Deceptive Placebo Treatment:

Based on our own research and the research of others, we consider the potential for positive clinical improvement from placebo to be a combination of multiple learning processes and environment cues that include: expectation, behavioral conditioning, adherence effects and the effects of a positive, supportive, compassionate and confident patient-physician relationship. We believe these four factors can be combined in a clinical intervention that is behaviorally tied to the taking of an inert substance (placebo pill) to produce what is commonly called “the placebo effect” without deception. We see the contributions of these fours components as follows:

Expectation: Positive expectations have been shown to induce placebo responses across a variety of conditions. (e.g., Benedetti et al 1999, Bausell et al 2006, Mondlock et al 2001, Linde et al 2007) including IBS. A recent study of IBS patients showed that saline infusion of rectal balloon intubation with positive expectation produced analgesia equivalent to rectal lidocaine infusion. (Verne et al 2003, cf. Vase et al 2001) While expectation can arise from just taking a medication in an RCT, multiple experiments have shown that positive expectations alone without any medication can produce significant clinical improvements (e.g., Thomas 1987; Olsson et al 1989). We believe that placebo pills given with positive expectations can have clinical impacts greater than these earlier experiments that just gave positive expectation without inert pills. We believe providing patients with information that demonstrates expectation works will enhance their expectations in a kind of “booth-strap” effect.

Conditioning: As stated in the mechanism discussion of the background section, part of the placebo effect is likely to be due to classical conditioning and is in independent of conscious expectation and belief. For example, almost all patients have experience taking medications that improve their symptoms (e.g., aspirin related compounds for headaches or fever). Thus Pavlovian conditioning may be responsible for some of the placebo response: previous medication (unconditioned response) + pill (conditioned response) allows for a subsequent positive response from the pill alone (conditioned response alone.) In fact, conditioning has been shown to influence immunological, endocrinal, intestinal and other bodily functions. (Pacheco-Lopez et al 2006) Importantly, Amanzio and Benedetti (1999) showed that the placebo effects of conditioning and expectation could be separated and are physiological distinct (expectation is nalaxone reversible and conditioning is not) and at times these effects act synergistically. In a subsequent experiment, this same team was able to show that conditioning is able to override verbal placebo expectations and that conditioning placebo response can happen completely unconsciously to decrease cortisol levels. (Benedetti et al 2003) We believe that a significant proportion of the placebo response in IBS is due to conditioning and that this process can be combined with the positive expectations to elicit placebo effects without deception. We propose that providing patients with information about such conditioning effects will contribute to positive response to our open-label placebo. In addition, explaining that the placebo effect may possibly involve a physiological “triggering” may prevent patients from feeling that the placebo response (or their illness) is “all-in-their head.”

Adherence: Multiple research experiments have shown that patients who adhere to treatment, even when that treatment is a placebo, have better outcomes than those who poorly adherent to placebo. (Horwitz & Horwitz 1993, cf. Granger et al 2005, Irvine et al 1999, Gallagher et al 1993, Czajkowski & Chesney 1990) A meta-analysis of the association between adherence to placebo therapy in eight RCTs with mortality as an endpoint (e.g. as post-myocardial infarction management, primary prevention of cardiovascular disease, and diabetes) showed that those in the placebo arms (19,633 participants) who adhered to taking placebo controls had a better outcome than those who did not take their placebo, (odds ratio 0.56, 95% CI 0.43 to 0.74). (Simpson et al 2006) It is likely that some of this adherence effect is due to a surrogate marker for other health promoting behaviors and attitudes and explanation of it potentially may contribute to positive expectations and conditioning effect needed to elicit the placebo effect.

Patient-Practitioner Relationship: Many studies indicate that the patient-practitioner encounter is a potent factor in health outcomes and a critical potentiating factor for placebo effects. (Kaptchuk 2002, Beck et al 2002, Steward 1995, Ong et al 1995, Kaplan et al 1989, Moerman 2003) For many non-life threatening illness, clear diagnosis, reassurance, and the patient-physician agreement about the nature of the problem hastens recovery or relief of symptoms. (e.g., Findler & Correa 1996, Bass et al 1986). A systematic review of the therapeutic impact of a positive patient-practitioner relationship found 25 eligible RCTs testing this question on physical conditions and found that “physicians who adopt a warm, friendly, and reassuring manner are more effective than those who keep consultations formal and do no offer reassurance.” (Di Blasi et al 2001) Our own recent RCT with IBS patients demonstrated that the patient-practitioner relationship is a significant component of the placebo response. (Kaptchuk et al 2008)

We hypothesize that these four factors – expectation, conditioning, adherence and a supportive patient- practitioner relationship can be operationally bundled together, explained to patients and elicit a clinically significant response to placebo treatment even when the placebo pill is given without deception.

7. Empirical Data Supporting Non-Deceptive Use of Placebos:

Our hypothesis for the efficacy of a non-deceptive placebo treatment is controversial and obviously requires empirical testing. However, the little direct empirical data that exist on this question– and it is very weak data -- supports our hypothesis. The only published study that we are aware of is an observational study of 15 patients with anxiety who were given placebo and told: “many people with your kind of condition have been helped by what are sometimes called ‘sugar pills, and we feel that a so-called sugar pill may help you too. Do know what a sugar pill is? A sugar pill is a pill with no medicine in it at all. I think this pill will help you as it has helped so many others.” (Park and Covi 1965) In this one-week study, only one patient was non-compliant and all 14 completers improved with the average initial patient registering 43% improvement on the anxiety scale used. Doctor rating averaged ‘quite a bit better” with all patients. The embedded qualitative exit interviews with subjects reported statements like: “the pills gave me moral support” or “I think that I had a lot to do with it myself, to be honest. By knowing myself that I had to control myself to keep myself in the right frame of mind.” Obviously, this study is poor evidence, especially given the absence of a treatment as usual control and the small numbers. Nonetheless, it suggests that our hypothesis merits rigorous testing.

A second “placebo dose extension study” provides further empirical support for our hypothesis that clinically-meaningful response to placebo can be produced without concealment or deception. Twenty-six children with attention deficit hyperactivity disorder (ADHS) were randomly assigned to one of two orders of experimental condition: 1) optimal dose of open-label stimulant medication (1 week) then 50% dose (1 week), then 50% dose + placebo (1 week) or 100% medication (1 week), then 50% dose + placebo, then 50% dose. (Sandler and Bodfish 2008) Children and parents/guardians were clearly told the inert nature of the placebo, how placebo pills help children with ADHD and all treatments were open-label to child and parents/guardians and single blind for teachers. In both arms, the symptoms remained the same when placebo was added to the 50% reduction but deteriorated when only 50% medication was received. Somehow full disclosure did not effect subvert a placebo effect. Both of these experiments are small but suggest that it may be possible to elicit a placebo effect without deception.

**C. Purpose of the Protocol**

Dramatic advances have been made in placebo studies. Recent studies suggest that placebo treatment not only can improve how you feel but also alter pathophysiology. Recent research indicates that a placebo response arises from learning processes and environmental cues that include positive expectation, behavioral conditioning, adherence effects, and a positive patient-practitioner relationship. Our own team has just completed a randomized controlled trial (RCT) in 262 patients with irritable bowel syndrome (IBS) which showed that placebo effects are real and have a genuine clinical impact, particularly when combined with a positive patient-practitioner relationship. (Kaptchuk et al 2008) Basic science research has demonstrated that placebo treatment elicits quantifiable changes in neurotransmitters, hormones, immune regulators and regionally specific brain activity that influences peripheral disease processes through plausible physiological mechanisms. (Miller & Kaptchuk 2008, Benedetti et al 2005, Pacheco-Lopez et al 2006) Despite these advances, harnessing such placebo effects clinically remains a challenge in part because of the belief that placebos can only elicit a response if the patient is unaware that they are receiving a placebo, such as in a double blind research protocol. Awareness of a placebo is thought to eliminate its efficacy. The widespread belief that concealment or deception is necessary to harness placebo effect creates a formidable barrier to using inert placebos in clinical practice because it is considered unethical to give a patient in a clinical situation a placebo that is deceptively described as a real drug. This randomized controlled trial seeks to critical challenge this assumption that deception is necessary to directly harness placebo effects by testing whether an open-label non-deceptive administration of placebo pills in the context of a supportive relationship can significantly improve the complaints of irritable bowel syndrome (IBS) patients compared to a treatment as usual control.

Besides the clinical need to seek novel therapies for IBS, this study has an ethical urgency. There are numerous indications that physicians are interested in harnessing placebo effects (American Medical Association 2006) and are already engaged using placebos in an unethical manner with deception. (e.g. Sherman and Hickner 2007, Hrobartsson and Norup 2003, Nitzan and Lictenberg 2004). To date, no study has adequately tested whether deception is required to obtain a placebo response. Our study seeks to test the hypothesis that direct placebo responses can be elicited without deception. In particular we hypothesize that open label placebo treatment without deception in the context of reassurance and positive expectation can provide significant clinical benefits for patients with IBS.

In this study, we will test whether placebo pills that are truthfully described “as inert substances (placebos) that have been shown in rigorous clinical tests to somehow produce significant self-healing processes in IBS patients” given in a context of positive expectation and reassurance can produce clinical improvement in patients with IBS. This study is a three-week RCT comparing non-deceptive open label placebo treatment to an observation waitlist control in 100 IBS patients. We believe this study involves no ethical compromise from normative ethical standards and could potentially result innovative treatment strategy for IBS patients and will ultimately give us preliminary data to support a more rigorous NIH RO1 grant.

**D. Aim:** To determine whether open-label non-deceptive placebo treatment in the context of positive expectation and a supportive and confident patient-practitioner relationship is significantly better than a no treatment + usual care control group matched for time.

**E. Hypothesis**: In IBS patients, a three weeks course of open-label non-deceptive placebo treatment in the context of positive expectation will be superior to no treatment plus usual care control.

#### F. DESCRIPTION OF RESEARCH PROTOCOL

#### Overview: This RCT seeks to determine whether non-deceptive (open-label) administration of placebo pill produces significantly more clinical improvement in IBS patients than an observation control.

#### Overall Design: Eighty patients with IBS will be randomized to a three-week course of either 1: non-deceptive open-label placebo pill in the context of positive expectation + usual care or 2. No treatment + usual care. Both groups will receive an equal amount of time with the practitioner. Patients will be assessed at baseline, mid-point and at the end of three weeks with the standard outcomes measures for IBS.

| Figure 1: Study Flow Chart  Open Label +usual care  (N=40)  No treatment waitlist+ usual care (N=40)  Baseline Evaluation and Randomization  (N=100)  Midpoint  Evaluation  Midpoint  Evaluation  3 Week Endpoint  Evaluation  3 Week Endpoint  Evaluation |
| --- |

Restatement of Research Question: A three-week course of non-deceptive open label placebo treatment will be produce statistically superior outcomes to a no treatment waitlist control group.

Design methodology and intervention:

Description of the non-deceptive placebo treatment arm: The intervention will

be geared to maximizing the contributions of positive expectation,

conditioning, adherence and a supportive and confident patient

practitioner relationship to the placebo response of IBS patients taking an

open-label placebo pill. The first phase of the discussion will be designed

to enhance expectation. Patients will be asked whether they have heard of

the placebo effect and what they think of it. After a brief exchange geared

to supporting any positive feelings the patient may have about placebo effects,

the practitioner will then talk about the evidence supporting the idea that just

taking placebo pills with a positive expectation initiates still poorly understood

effects that can have a profound impact of illness. It will be clearly explained that

placebo are made of "inert" substances like sugar pills but have been show

in clinical trials to improve patient symptoms. The practitioner will discuss

our published meta-analysis that showed on average 42% of patients on placebo treatment improve in IBS RCTs (Patel et al 2005). Furthermore, the patients will be informed about our recent IBS study showing that placebo acupuncture was as effective as current medications for IBS but without the side effects. Also during this discussion, to support expectation and to insure that patients are not conflicted about placebo improvement somehow being a sign that the IBS is “in their heads,” the physician or nurse practitioner will also explain that placebo effects change human physiology and can improve immune, endocrine, and pain mechanisms and that response to placebo is a demonstration of “self-healing capacities.” During the discussion the treating physician or nurse practitioner will naturally and clearly repeat the words that are stated in the informed consent that informs the patient that he/she will receive “an inert substance (the placebo), something like a sugar pill, that has been shown in rigorous clinical tests to somehow produce significant self-healing processes in IBS patients.”

The treatment will also seek to maximize the contributions of adherence

and conditioning to the placebo effect of IBS. Patients will be told that it is critical

to take the pill two times daily with meals and that scientific evidence suggests

that the positive effects of the pill taking will only happen if one is meticulous

about taking the pill. Patients will be asked to describe situations in their life

where taking pills had positive effects in their lives. When such a situation is

remembered, patients will be encouraged to remember this context when

they’re taking their inert medications. To again take any negative

connotation about “the symptoms are in their head” patients will be informed

about how conditioning with pills can “automatic trigger” a conditioning

response like Pavlov’s dog who salivate to a bell. The entire patient-

practitioner encounter will take place in the context of a positive, confident

and supportive relationship. As much as possible, we will follow the protocol

used in our last RCT and to ensure that the interaction includes each of

the following points: the conveyance of a warm and friendly manner,

definite communications of empathy, behaviors that demonstrate

active listening, and an empathic expression of confidence in the likelihood

of improvement when taking pills, even inactive pills. A warm manner will have

the following characteristics: hand shaking, exchange on whether to use first or

last names, eye contact but not over gazing, courtesy, friendliness, orienting

the patient during examination, time for questioning, head nodding, forward

leaning, and uncrossed legs and arms. Empathy will be invoked with the

physician stating how he/she understands the difficulties that people with IBS

live with. Confidence will be fostered as the practitioner explains the

evidence concerning placebo effects. At the end of the first visit the patient will

be given enough placebo for the first half of the study and a mid-point follow-up

will be scheduled. The mid-point follow-up will be similar to the baseline

but abbreviated in time and will also include scheduling a final evaluation.

The entire discussion will take approximately 20 minutes.

Description of the no treatment usual care control arm:

The purpose of this arm is to match the ‘active” arm for time with practitioner. In

the informed consent, patients will be told that they will be randomized into

either the placebo or no treatment waitlist usual care arm. It will be explained,

if they are randomized to the latter, they will continue their regular IBS regimen

and will contribute to the observational IBS group. During the visits, t

he practitioners will seek clear descriptions of the patient’s symptoms

and life-style in relationship to their IBS. This evaluation will be in an identical context of the “active” arm with the exception that no attempt will be made to marshal positive expectation, conditioning response, or confidence of improvement or adherence to their IBS regimen. In order to fill the 20 minutes, the physician or nurse practitioner will provide educational support concerning IBS and go over the patient’s knowledge of IBS and how their life-style, including diet, exercise and stress contributes to their symptoms. We also review their current therapeutic regimen for IBS but we will not attempt to alter it during the study period.

Fidelity of treatment: To monitor fidelity to the time of treatments, the physician or nurse practitioner will put on a timer before the patient enters the room and turn off the timer after she/he leaves and record the time on the chart.

Randomization- Group assignment will be determined based on results from program “Research Randomizer”. Randomization number will be given at time of visit. Allocation to group will be blinded until patient encounters the practitioner.

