**Statistical Power**

Our previous trial of placebo effects in IBS produced effect sizes that ranged from d=.5 to d=.9. Using two-tailed t-tests with alpha set at .05, a total sample size of 80 will have 60% power to detect the lower end of this range and 94% power to detect the upper end of the range. Using the same assumptions but a total sample size of only 50, we would have power between 41% and 88%.

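### The protocol gives two trial sizes, 80 and 100, and the two arms of 40 in Figure 1 do not add up to the 100 in its randomisation box

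*Protocol*

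**What the plan says.** The total appears in five places in the Protocol, and Figure 1 also gives arm sizes.

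- Section A (Purpose of Protocol): "to an observation waitlist control in 80 IBS patients".
- Section C (Purpose of the Protocol), in a sentence that otherwise nearly repeats section A: "to an observation waitlist control in 100 IBS patients".
- Section F, Overall Design text: "Eighty patients with IBS will be randomized to a three-week course of either".
- Section F, Figure 1, top box: "Baseline Evaluation and Randomization (N=100". Below it are two arms of 40 each, the control arm reading "No treatment waitlist+ usual care (N=40".
- Statistical Power: the calculation is for "a total sample size of 80", with a second scenario at a total of 50.

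The protocol describes two arms only. It mentions no run-in, no third group, no allowance for dropout and no expected number of screening failures.

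**The concern.** The number to be randomised is a basic element of a protocol. It sets the recruitment target and tells everyone when enrolment is complete. Here two numbers stand in current text, and the flow chart disagrees both with the design sentence beside it and with its own arms.

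The number also bears on power. At the lower end of the sponsor's own effect-size range, moving between 80 and 100 changes power by about 10 percentage points. A reader needs to know which total the quoted power refers to and whether that is the total the trial will randomise.

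**Working it through.** **Step 1. Add the arms.** 40 + 40 = 80. The box above them says 100, so 100 − 80 = 20 patients have no stated destination.

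**Step 2. Find which total the power statement uses.** Inputs, all from Statistical Power: two-tailed t-test, alpha 0.05, d from 0.5 to 0.9, total 80 (stated power 60% and 94%) and total 50 (stated power 41% and 88%). Allocation is taken as 1:1, as in Figure 1.

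With n per arm, the noncentrality is d × √(n/2) on 2n − 2 degrees of freedom. Power is the probability that a noncentral t variable falls beyond the two-sided 5% critical value.

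At d = 0.5:

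- Total 80 (n = 40): 0.5 × √20 = 2.236 on 78 df, power 59.8%.
- Total 100 (n = 50): 0.5 × √25 = 2.500 on 98 df, power 69.7%.

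The normal approximation can be followed by hand: 2.236 − 1.960 = 0.276 gives 60.9%, and 2.500 − 1.960 = 0.540 gives 70.5%.

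| Total N | Power, d = 0.5 | Stated | Power, d = 0.9 | Stated |
|---|---|---|---|---|
| 50 | 41.0% | 41% | 87.7% | 88% |
| 80 | 59.8% | 60% | 97.8% | 94% |
| 100 | 69.7% | none | 99.4% | none |

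The stated 60% reproduces at 80 and not at 100. Both figures for a total of 50 reproduce as well, so the method is the one the sponsor used. The 94% at d = 0.9 does not reproduce at 80 (97.8%). It does not point to 100 either (99.4%). That is a separate discrepancy and plays no part in this point.

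**Step 3. Look for an explanation of the 20.**

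- *100 evaluated, 80 randomised.* The Figure 1 box covers randomisation as well as baseline evaluation, and section C speaks of the comparison itself in 100 patients.
- *100 randomised to leave 80 after 20% loss.* The arithmetic fits, since 80 / (1 − 0.20) = 100. But the design sentence says that eighty are randomised, and no loss rate is given.
- *A faulty reading of the figure.* The boxes were read out of order, but the 100 directly follows the randomisation label, and section C gives 100 independently in running prose.

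None of these is stated in the protocol, so the text does not reconcile the two numbers.

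**The case against.** The strongest reply is that the operative number is hardly in doubt. The randomisation sentence, both arm sizes, the opening purpose section and the power calculation all say 80. Against them stand one sentence in a second purpose section and one figure box. This largely stands: the power statement was built on 80, and the repair is small. It does not remove the conflict, because the document never says that the 100s are superseded.

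It can also be said that the t-test comparison does not measure the effect on the primary analysis, which is a chi-square test of IBS-GIS responders. That is right. The t-test is used here because it is the sponsor's own calculation and shows which total lies behind it. As an illustration only, suppose the adequate-relief rates of 62% and 28% quoted in the background from the sponsor's earlier trial applied to the responder endpoint. Power would then be about 88% with 80 patients and 94% with 100.

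Two stronger readings are tempting, and the document supports neither.

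- A reader might infer from Figure 1 that 20 randomised patients are discarded, so that analysis by randomised group fails. No text says that any randomised patient is removed or left out of the analysis.
- A reader might infer that dropout will take the trial below its planned power. The protocol gives no loss rate, so the size of any such effect would rest on an assumption. Statistical Power also already reports power for a total as low as 50.

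**Conclusion.** The protocol contradicts itself on the number to be randomised: 80 in section A, the Overall Design text, the sum of the arms and the power statement; 100 in section C and the Figure 1 randomisation box. The gap is 20 patients. At d = 0.5 it corresponds to 59.8% against 69.7% power; at d = 0.9 the difference is small (97.8% against 99.4%). These values assume 1:1 allocation and the sponsor's two-sided t-test at 0.05.

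That 80 is operative and the 100s are uncorrected is the likeliest reading, resting on the reproduced 60% and on the weight of the other statements. Only the sponsor can confirm it. The point is an error in a figure that the trial relies on, cheap to correct. It is not evidence of a flaw in the analysis.

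**What to change.** State one number to be randomised and use it everywhere.

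- **If 80 is intended** (the likely case): change 100 to 80 in section C and in the Figure 1 randomisation box. Nothing else moves, and the power total stays at 80.
- **If 100 is a screened or consented number:** show it in its own labelled box above randomisation, put 80 in the randomisation box, and correct section C, which now describes the comparison as made in 100.
- **If 100 are to be randomised:** show 50 + 50 in Figure 1, change section A and the Overall Design sentence, and restate power for 100 (69.7% at d = 0.5 and 99.4% at d = 0.9 by the same t-test).

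The first option costs one number in a sentence and one in a figure. The second adds a labelled box. The third also changes the recruitment target and the power paragraph.
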